### Study procedure

Figures 4 and 5 present an overview of the study procedure. The urologists will refer potentially suitable cases to the researchers. Subsequently, the researchers will determine whether these patients meet the inclusion criteria by reviewing their medical records and conducting interviews based on a question regarding urinary incontinence experience. The researcher will explain the purpose and process of the study to the patients who meet the inclusion criteria and invite them to participate in this investigation. After patients agree to participate and sign the consent form, they will complete the pretest questionnaire in a private area. Next, the researcher will open the random assignment envelope prepared by the principal investigator and assign the patients to either the experimental group or the attention control group. The experimental group will undergo a 12-week SMI-UI in addition to routine care, whereas the attention control group will receive routine care and a dietetic education information package. After posttests 1 and 2, data will be collected from the two groups at 12 and 16 weeks after the pretest, respectively. With the assistance of the researchers, the mobile self-management application will be installed on the smartphones or tablets of patients in the experimental group. In accordance with the steps for the operation of the application outlined in the self-management handbook, the patients will be taught to use the application. Thereafter, the researcher will provide each patient with SMI-UI activities for a duration of 12 weeks. Patients in the attention control group will be provided with a dietetic education information pack for home learning. Face-to-face post-test 1 and post-test 2 will be scheduled during patients’ follow-up visits. In a few cases where the timing of outpatient visits are outside of data collection hours, paper questionnaires will be mailed with the patient’s consent. As a token of appreciation for their contribution to the research, participants will receive a gift voucher worth NT$100 each time they complete a questionnaire.

### Management and monitoring of intervention fidelity

In this study, an Intervention Provider Handbook, a Case Interaction Record, and a research handbook will be developed. Explanatory meetings and training courses will be organized for the researchers to ensure that they clearly understand the study design, methods, processes, and relevant precautions. The SMI-UI will be performed by a trained nurse who will complete the required training before providing the intervention (intervention provider). In addition, the intervention provider will be required to complete the Case Interaction Record immediately after each session of professional support. The principal investigator will regularly review the interaction record form to assess the consistency and correctness of the provided intervention. The researcher will evaluate the time that individual patients spend reading the multimedia information and the e-handbook on the mobile self-management application and will invite patients to record the status of their urinary incontinence and the implementation frequency of PFME by using the application. The intervention provider will ask the patients some questions in each interaction to assess how they are learning about and implementing the intervention. The confidence of patients in applying new knowledge or skills to daily life will also be assessed through questions regarding self-management confidence (0–10 points). For those with a score of < 7 points, the unclear points will be clarified [18].

### Ethical considerations

This study has been approved by the institutional review board of the hospital recruiting individual patients (approval number: 201902235B0C505). The research plan will be registered before initiating the recruitment of the first research case (ClinicalTrials.gov ID: NCT05335967). The researchers will abide by the research ethics guidelines and maintain the privacy of patients (i.e., the identity of patients will be encoded). All patients will have the right to withdraw from the study at any time with no effect on their original treatment. The collection of research data is for academic purposes only.

### Data management and dissemination of results

The research data will be stored in the office of the principal investigator. The electronic files will be stored on a password-protected computer, and hard copies of the questionnaires and consent forms will be separately placed in opaque, locked cabinets. A researcher will input the questionnaire data into the IBM SPSS Statistics, and then two researchers will validate that the data have been entered correctly. Before the researchers perform statistical analysis, they will use descriptive statistics to understand the data distribution and confirm the absence of anomalous scores. The research results will be submitted to international peer-reviewed journals and conferences and provided to participants who are interested in them.

### Power analysis and sample size

Cohen’s *f* represents a standardized measure of the average effect [64] therefore, it is not affected by the varying score ranges of each scale. Based on the results of a previous study, the effect size f is 0.27 for the outcome variable of self-efficacy [65]. The sample size of this study was estimated using G*Power, with α = 0.05 and power = 80% according to repeated-measure analysis of variance (ANOVA) with two groups and three measurements. This study requires a sample size of 74 [66]. Based on this information and considering a study discontinuation rate of 17–18% [67], we plan to include a total of 86 patients (43 per group) in this study.

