### Data analysis plan

All patient data will be included in the analysis. IBM SPSS Statistics (version 20.0; IBM Corp., Armonk, NY, USA) will be used to perform statistical analysis. Descriptive statistics (e.g., mean, standard deviation, median, frequency, and percentage) will be used to present data. The homogeneity of basic attributes, disease treatment variables, and outcome variables in the experimental and attention control groups at the pretest stage will be assessed through independent sample *t* tests and chi-squared tests. The effect of the intervention will be determined using a generalized estimating equation. Two-tailed tests will be used, and *P* values ≤ 0.05 will denote statistically significant differences.

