This study began in May 2022, but because of the COVID-19 pandemic, many hospital beds had to be reassigned to patients with COVID-19, and nonemergency surgery and medical treatment had to be postponed or delayed in accordance with the national and hospital pandemic prevention policies. Therefore, the number of patients who underwent surgical treatment was considerably lower than that recorded before the pandemic [68]. The inclusion period for this study definitely therefore needs to be extended to reach the desired sample size to provide sufficient statistical power.

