### Current study status

At the time of this submission, 68 of 90 participants have been recruited and randomized into two groups.

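### The enrolment target of 86 does not follow from 74 patients and 17–18% discontinuation, and the article elsewhere counts recruitment against 90

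*Protocol article*

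**What the plan says.** The section Power analysis and sample size takes an effect size from an earlier study ("the effect size f is 0.27 for the outcome variable of self-efficacy") and computes the size "with α = 0.05 and power = 80% according to repeated-measure analysis of variance (ANOVA) with two groups and three measurements". The result is given as "This study requires a sample size of 74". The next step allows for loss: "considering a study discontinuation rate of 17–18% [67], we plan to include a total of 86 patients (43 per group) in this study".

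The section Current study status, at the end of the Discussion, reports that "68 of 90 participants have been recruited and randomized into two groups". The Discussion also says that the inclusion period "needs to be extended to reach the desired sample size to provide sufficient statistical power", without naming the size that is meant. Nothing in the article explains a move from 86 to 90.

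**The concern.** A reader who takes 74 as the number to retain and 17–18% as the expected loss cannot arrive at 86. If recruitment stopped at 86 and patients left at the assumed rate, the trial would end slightly below the size on which its 80% power rests. In addition, a status count of 68 out of 90 reads naturally as progress towards a target, and that target is not the one in the sample size section. Recruitment was still open when the article was submitted, and power is the reason given for a longer inclusion period, so the published plan should say plainly where recruitment ends. With both 86 and 90 in print, the final report could look like over-recruitment or under-recruitment, depending on which figure it is compared with.

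**Working it through.** **Inputs.** From Power analysis and sample size: f = 0.27, α = 0.05, power 80%, two groups, three measurements, required size 74, discontinuation 17–18%, planned total 86 (43 per group). From Current study status: 90. From Random assignment: 1:1 allocation. Not stated: the correlation between repeated measurements, and whether the ANOVA tests the between-group effect or the interaction. Both are assumptions below.

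**Step 1. Reproduce 74.** For the between-group effect with m measurements and correlation ρ, the noncentrality is λ = f²·N·m / (1 + (m − 1)ρ), on 1 and N − 2 degrees of freedom. With f = 0.27, m = 3, ρ = 0.5 and N = 74:

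λ = 0.0729 × 74 × 3 / 2 = 8.09, power 0.801.

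The smallest even N that reaches 80% is 74, so the figure is reproduced. With the interaction test and ρ = 0.5 the required N would be only 24, so the between-group reading is the one that fits. The base figure of 74 is not in question here.

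**Step 2. Allow for loss.** To retain n patients at loss d, enrol n/(1 − d).

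- d = 17%: 74/0.83 = 89.2, so 90.
- d = 17.5%: 74/0.825 = 89.7, so 90.
- d = 18%: 74/0.82 = 90.2, so 91, or 92 for equal groups.

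The stated 86 is 4 to 5 below this (6 below 92). Multiplying by 1 + d, a common shortcut that under-corrects, gives 74 × 1.17 = 86.6 and 74 × 1.18 = 87.3. So 86 may be the first of these rounded down, but the article does not show its formula.

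**Step 3. What each target delivers.**

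| Enrolled | Left at 17% loss | Left at 18% loss | Largest loss that keeps 74 |
|---|---|---|---|
| 86 | 71.4 | 70.5 | 1 − 74/86 = 14.0% |
| 90 | 74.7 | 73.8 | 1 − 74/90 = 17.8% |
| 92 | 76.4 | 75.4 | 1 − 74/92 = 19.6% |

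The tolerated loss for 86 lies outside the stated range. For 90 it lies inside.

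**Step 4. Effect on power.** Same formula as in step 1, over a range for the unstated correlation:

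| ρ | N = 74 | N = 71 | N = 70 | Drop from 74, in points |
|---|---|---|---|---|
| 0.3 | 0.881 | 0.867 | 0.862 | 1.4 to 1.9 |
| 0.4 | 0.841 | 0.825 | 0.820 | 1.6 to 2.1 |
| 0.5 | 0.801 | 0.785 | 0.779 | 1.7 to 2.3 |
| 0.6 | 0.763 | 0.745 | 0.739 | 1.8 to 2.4 |
| 0.7 | 0.726 | 0.708 | 0.702 | 1.8 to 2.5 |

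The drop is about 1.5 to 2.5 points whatever the correlation. The level of power depends far more on the correlation than on the missing 3 or so patients.

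**The case against.** The strongest reply is that little turns on this. The Data analysis plan includes all patient data and uses a generalized estimating equation, so a patient lost between the 12-week and 16-week tests still contributes the 12-week result. Counting every discontinuation as a wholly lost patient is therefore a conservative bound. The study is also presented as a feasibility study, and if 90 is the working target the shortfall is nil at 17% and a fraction of a patient at 18%.

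Much of this stands, and it limits the weight of the point. It does not remove it. The sample size section itself inflates 74 for discontinuation, so the plan treats 74 as the number to keep. Patients with a pretest only would add little to the estimate of effect. No choice of analysis model makes 86 follow from 74 and 17–18%, or reconciles 86 with 90. The article does name a primary efficacy outcome, gives a formal power calculation and appeals to power when it discusses recruitment. Nor is this a detail that an article leaves to a fuller document: both totals are printed, and one conflicts with its own inputs.

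Three stronger readings are tempting and are not supported. A reader might infer that recruitment had already been extended and that its end was being chosen freely. The Discussion says only that an extension is needed, and no interim look at outcomes is described. A reader might infer that 90 is exactly right for the stated range, but at 18% it leaves 73.8, just under 74. And a reader might take 78% as the plan's own power at the expected loss, but that value rests on a correlation that the article does not give.

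**Conclusion.** The point holds as a minor error of arithmetic together with an unreconciled target. From the plan's own printed figures, with no further assumption, 86 falls about 3 patients short of 74 at the stated discontinuation and protects 74 only up to 14.0% loss. The two totals, 86 and 90, stand in the same article without explanation, and 90 fits the stated inputs better.

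The cost in power is about 2 percentage points: from 80.1% to about 78%, assuming the between-group test and a correlation of 0.5, and treating every discontinued patient as lost altogether. Use of partial data would make it smaller. It would be wrong to conclude that the trial is seriously underpowered. The hypothesis and the analysis method are unaffected.

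**What to change.** State one enrolment target in both Power analysis and sample size and Current study status, show the formula 74/(1 − d), and explain the change from 86. Either of these would do:

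- Use 90 (45 per group) and state that it keeps 74 patients up to 17.8% loss. If the full range is to be covered, 92 (46 per group) does so at 18%.
- Keep 86 (43 per group), state that it keeps 74 only up to 14% loss and that power is slightly below 80% at 17–18% loss, and correct the 90 in Current study status.

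If a power figure is printed, give the correlation and the effect tested alongside it. The first option with 90 is a change of wording only, since recruitment is already reported against 90. Choosing 92 would add two patients to that figure.

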### Data analysis plan

All patient data will be included in the analysis. IBM SPSS Statistics (version 20.0; IBM Corp., Armonk, NY, USA) will be used to perform statistical analysis. Descriptive statistics (e.g., mean, standard deviation, median, frequency, and percentage) will be used to present data. The homogeneity of basic attributes, disease treatment variables, and outcome variables in the experimental and attention control groups at the pretest stage will be assessed through independent sample *t* tests and chi-squared tests. The effect of the intervention will be determined using a generalized estimating equation. Two-tailed tests will be used, and *P* values ≤ 0.05 will denote statistically significant differences.

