### Discontinuation criteria

After the patients agree to participate in this research, the intervention will be discontinued if they meet any of the following conditions: (1) A physician determines that pelvic floor muscle exercise (PFME) is not suitable for the patient. (2) The patient meets the exclusion criteria. (3) The patient has not experienced urinary incontinence for 1 week or longer prior to the start of the intervention. (4) The patient perceives an improvement in their symptoms of urinary incontinence prior to the commencement of the study. Therefore, although they still experience episodes, they may choose not to participate in the study.

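### The only named effect analysis is a GEE with no pretest or stratum term, under 17–18% expected loss; an adjusted repeated-measures model valid under missing-at-random would be safer and more precise.

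*Protocol article*

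**What the plan says.** The protocol article's Data analysis plan fixes the method in one sentence: "The effect of the intervention will be determined using a generalized estimating equation". It adds "All patient data will be included in the analysis". Neither the pretest score nor the randomisation stratum is named as a term in the model.

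Power analysis and sample size allows for loss: "considering a study discontinuation rate of 17–18% [67], we plan to include a total of 86 patients (43 per group". This gives a size only. It does not give the cause, the timing or the split by arm.

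Discontinuation criteria says that "the intervention will be discontinued if they meet any of the following conditions", then lists four. They include "A physician determines that pelvic floor muscle exercise (PFME) is not suitable for the patient", "The patient has not experienced urinary incontinence for 1 week or longer prior to the start of the intervention" and "The patient perceives an improvement in their symptoms of urinary incontinence prior to the commencement of the study".

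Random assignment stratifies by time since surgery (0–6, 7–12 and 13–24 months). Study procedure places the pretest before the envelope is opened and the posttests at 12 and 16 weeks, with mailed questionnaires for some visits.

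**The concern.** Unweighted GEE uses the responses that happen to be observed. It is in general guaranteed unbiased only if loss is unrelated to the scores, or related only through covariates in the model. With an independence working correlation, nothing links a patient's missing posttest to that patient's earlier scores. If the patients who leave differ in those scores, and differ in opposite directions or to a different extent by arm, the estimated effect shifts. Including all patient data does not prevent this, because the week-12 and week-16 scores of those who leave are not there to include.

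Uneven loss is conceivable here. The experimental arm has 12 weeks of weekly calls and app recording; the control arm has a single information package. The outcome at stake is the primary one, cancer-related self-efficacy.

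There is also a plain loss of precision. The pretest is collected before randomisation and the strata are known, but the stated analysis does not use either as a covariate.

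**Working it through.** **1. The plan's own figure.** Inputs from Power analysis and sample size: f = 0.27, α = 0.05, power 80%, two groups, m = 3 measurements. The correlation ρ is not stated. For the between-group test, λ = f²·N·m / (1 + (m − 1)ρ). With N = 74 and ρ = 0.5, λ = 0.0729 × 74 × 3 / 2 = 8.09 on 1 and 72 degrees of freedom, which gives power 0.801. So 74 reproduces at ρ = 0.5 (ρ = 0.4 gives 68, ρ = 0.6 gives 82), and 0.5 is used below as an assumption. In standardised units, d = 2f = 0.54.

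**2. Expected observed numbers.** 86 × (1 − 0.17) = 71.4 and 86 × (1 − 0.18) = 70.5, so about 71 of 86.

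**3. Large-sample bias.** Assumptions: Gaussian outcome, three visits, ρ = 0.5, about 17% lost by the last visit, log-odds slope of 1 per SD where loss depends on scores, 400,000 patients per arm, true difference 0.50 SD. Estimated difference at the last visit:

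| Loss pattern | GEE independence | GEE exchangeable | GEE unstructured | Likelihood model, unstructured |
|---|---|---|---|---|
| Completely random | 0.50 | 0.50 | 0.50 | 0.50 |
| Depends on earlier scores, same in both arms | 0.50 | 0.50 | 0.50 | 0.50 |
| Depends on earlier scores, opposite by arm | 0.34 | 0.495 | 0.493 | 0.50 |
| Depends on unseen scores, opposite by arm | 0.26 | 0.35 | 0.35 | 0.35 |

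Only the third row separates the methods in a way that the choice of model can repair: 0.34 − 0.50 = −0.16 SD for independence, and less than 0.01 SD for the other structures. In the fourth row the likelihood model is no better than GEE with a non-independence correlation.

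**4. Bias at the trial's size.** Assumptions: 86 patients, ρ = 0.5, no true effect, 1,500 trials, 26% loss in the experimental arm depending on the pretest and 10% in control (average 18%). Week-12 result:

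| Analysis | Bias (SD) | False positives |
|---|---|---|
| GEE independence, group-by-time | −0.139 | 9.5% |
| GEE exchangeable, group-by-time | −0.004 | 5.4% |
| Pretest-adjusted normal model | 0.003 | 4.5% |

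The first bias is 0.139 / 0.54 = 26% of the planned effect. A re-run with assumed loss of the same kind gave about −0.10 SD for independence GEE and about 0 for the other two. Simulation error on the false-positive rates is about ±1 percentage point.

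**5. Precision.** With random loss of 17.5%, 43 × 0.825 = 35.5 patients per arm are observed at week 12. In SD units:

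- Group-by-time contrast (change from pretest): variance per patient 2(1 − ρ) = 1.00, so SE = √(2 × 1.00 / 35.5) = 0.237.
- Pretest-adjusted contrast: variance per patient 1 − ρ² = 0.75, so SE = √(2 × 0.75 / 35.5) = 0.206.

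Simulated mean SEs were 0.228–0.234 without pretest adjustment and 0.201–0.206 with it. The reduction runs from 1 − 0.206/0.228 = 10% to 1 − 0.201/0.234 = 14%. The gain comes from the covariate and appears with GEE and with a normal model alike. It depends on ρ: the ratio of the two SEs is √((1 + ρ)/2), a reduction of 19% at ρ = 0.3, 13% at 0.5 and 8% at 0.7.

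**The case against.** GEE is an accepted method for this design, and working correlation and missing-data handling are often left to an analysis plan that is not shown. Their absence from the article is not an error. In the adverse case at the trial's size, exchangeable GEE is unbiased for practical purposes, so the harm belongs to the independence structure, which the article does not choose. The harmful loss patterns are assumptions. All of this stands.

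Three stronger readings are tempting, and the documents do not support them.

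- A reader might infer that the plan expects loss tied to patient status. It gives 17–18% as a size only. The discontinuation criteria stop the intervention and do not say that outcome measurement stops. The criterion on perceived improvement precedes study commencement, and the one on absence of incontinence precedes the intervention, so neither can be a response to the treatment received. Mailed questionnaires may also limit missed assessments.
- A reader might infer that GEE must give way to a mixed model. A sensible working correlation, weighted GEE or multiple imputation would also meet the concern, and a mixed model gives no protection when loss depends on unseen scores.
- A reader might infer that the robust Wald test is materially too liberal at this size. With random loss the two GEE versions rejected 5.7% and 6.3% of the time against 5.3% for the normal model, which is within simulation error.

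What remains is that the one named analysis is not assured under the weaker missing-at-random assumption, and that it does not use the pretest or the strata as covariates.

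**Conclusion.** The point holds as a modest improvement to the stated analysis, not as an error that invalidates it. Under assumed arm-differential loss depending on earlier scores, independence GEE is biased by about −0.10 to −0.16 SD. The bias is nil if loss is random or follows the same pattern in both arms, and below 0.01 SD with exchangeable or unstructured correlation. The article does not show which case applies.

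The precision gain needs no assumption about why patients leave. At ρ = 0.5, a 10–14% smaller standard error is worth roughly 22–35% more patients for the week-12 contrast (1/(0.206/0.228)² = 1.22; 1/(0.201/0.234)² = 1.36). The size of that gain rests on the assumed ρ and on comparison with a group-by-time term.

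**What to change.** For the continuous scale scores, make the primary analysis of posttests 1 and 2 a repeated-measures model valid under missing-at-random. Either of these would serve:

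- a linear mixed model with unstructured covariance, or
- GEE with a stated non-independence working correlation, whose validity under missing-at-random relies on that correlation being close to right.

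Adjust for the pretest score and the time-since-surgery stratum, include all randomised patients, and state the missing-data assumption. Keep the plain GEE as a sensitivity analysis.

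The cost is wording: no new data are needed and the evaluable sample size of 74 does not change. The small downside, if the mixed model is chosen, is a distributional assumption that robust GEE avoids. The status paragraph reports 68 of 90 patients recruited at submission. The change should be dated and fixed before outcome data are examined by arm.
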